#### Implementation

Implementation outcomes focus on domains of the RE-AIM framework including at the program, center, and individual level (Table 3).

**Table 3 Tab3:** Implementation outcomes for Hypertension Treatment in Nigeria Program

RE-AIM Domain: Definition	Level	Type	Outcome
Reach: Absolute number, proportion, and representativeness of sites and individuals who participate in the HTN Program	Program	Quantitative	• Number of participating PHCs/total number of selected PHCs in the Federal Capital Territory
	Center	Quantitative	• Diversity of participating PHCs and staff in terms of size, ward, baseline staffing levels
		Qualitative	• Reasons for non-participation of selected PHCs in the Federal Capital Territory • Reasons for adult patients to have not been screened for high BP within participating PHCs within the past 3 working days
	Individual	Quantitative	• Number of adult patients with BPs measured / total number of adult patients within participating PHCs within the past 3 working days • Differences in sociodemographic (e.g., age, sex, geography) characteristics between registered patients and individuals in the clinic catchment areas based on concurrently collected or community-based survey data • Diversity of registered patients receiving care at participating PHCs for HTN diagnosis and management by age, sex, ward, and education
Effectiveness: The impact of the HTN Program on treatment and control rates	Program	Quantitative	• Treatment rate within the overall system of participating PHCs defined by 6-month rolling average • Control rate within the overall system of participating PHCs defined by 6-month rolling average • Mean systolic blood pressure and diastolic blood pressure within the overall system of participating PHCs defined by 6-month rolling average and based on last visit
	Center	Quantitative	• Median and/or mean treatment rate across participating PHCs defined by 6-month rolling average • Median and/or mean control rate across participating PHCs defined by 6-month rolling average • Mean SBP and DBP across participating PHCs defined by 6-month rolling average and based on last visit
		Qualitative	• Reasons for variation in treatment rates between participating PHCs • Reasons for variation in control rates between participating PHCs • Reasons for variation in mean systolic and diastolic blood pressure between participating PHCs
Adoption: Absolute number, proportion, and representativeness of sites who are willing to initiate the HTN Program	Program	Quantitative	• Percentage of PHCs using the hypertension patient registry in the last 3 months • Percentage of patients treated with fixed-dose combination therapies in the last 3 months
		Qualitative	• Reasons for variation in registry use among participating PHCs at 3 months after site initiation • Reasons for variation in use of fixed-dose combination therapies in the last 3 months • Adoption of team-based care among participating PHCs, and reasons for success or challenges
Implementation: Fidelity to the HTN Program protocol, including consistency of delivery as intended. Time and cost of the intervention, and use of the intervention strategies	Program	Quantitative	Fidelity (Implementation) • Proportion of selected PHCs who participated in baseline hypertension training • Proportion of selected PHCs who participated in site initiation training • Proportion of selected PHCs who received at least one supportive supervision visit in the past 7 months • Proportion of selected PHCs who received an audit and feedback report within the past 3 months • Percentage of PHCs with a working blood pressure monitor at the site on the day of assessment • Percentage of PHCs with blood pressure medicines available on the day of assessment • Percentage of patients with step up indicated who received step up treatment in the last 6 months Cost • Modeled direct HTN Program costs based on staff, BP machines, data capture, data analysis, and BP lowering drugs for hypertension diagnosis, treatment and control overall, for each PHC and per patient
	Program	Qualitative	Fidelity (Implementation) • Reasons for variation in fidelity measures • Reasons for variation in availability of essentials medicines and equipment • Reasons for variation in fidelity to the step up treatment protocol Cost • Acceptability of upfront and ongoing HTN Program costs among stakeholders, including within Federal Ministry of Health
	Center	Quantitative	Fidelity (Intervention) • Number and proportion of adult patients with hypertension who are registered/total number of adult patients with elevated blood pressure within participating PHCs within the past 3 working days • Monthly proportion of registered patients with appropriate stepped care/total number of registered patients • Monthly proportion of registered patients treated with fixed-dose combination therapy/total number of patients on treatment
	Center, Individual	Qualitative	Fidelity (Implementation) • Reasons for adult patients with hypertension to have not been registered within participating PHCs within the past 3 working days
	Individual	Quantitative	Cost • Modeled monthly and annual out-of-pocket drug costs for hypertension treatment
	Individual	Qualitative	Acceptability • Reasons for variation in acceptability, satisfaction, and perceived quality of care at patient-level • Trust in primary health care system Cost • Acceptability of upfront and ongoing hypertension diagnosis and treatment costs among patients with hypertension
Maintenance: The extent to which the HTN Program becomes institutionalized or part of the routine organizational practice	Center	Quantitative	Maintenance • Proportion of participating PHCs who maintain treatment rates above baseline rates at 6, 12, 24, 36, and 48 months • Proportion of participating PHCs who maintain control rates above baseline rates at 6, 12, 24, 36, and 48 months • Proportion of participating PHCs without blood pressure medication stockouts at 36 and 48 months • Proportion of participants retained in care at participating PHCs at 6, 12, 24, 36, and 48 months
		Qualitative	Maintenance • Reasons for variation in maintenance of treatment rates above baseline rates • Reasons for variation in maintenance of control rates above baseline rates • Reasons for variation in sustainment of blood pressure medication supplies • Reasons for variation in proportion of participants retained in care at PHCs
	Individual	Qualitative	Maintenance • Reasons for remaining in care and on treatment within the PHC

*Abbreviations*: *BP* Blood pressure, *HTN* Hypertension Treatment in Nigeria, *PHC* Primary health care center

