Performance and Quality Reporting	December 2020	60	Health Clinic	Monthly performance and quality reports are issued to each participating site to summarize key metrics, aggregated over a rolling 3-month period. Metrics include treatment, control, and retention rates, along with lists of patients for targeted follow-up. Comparisons are made with other sites in the HTN Program.	Data quality audits are conducted during supportive supervision visits to compare data between the paper and electronic case report forms, and correct errant data points. Study team members communicate with sites on a quarterly basis to follow up on performance reports and ascertain if the site has reviewed and understood the report. In interim and final qualitative evaluations, sites will be asked for their feedback on the performance reports.
Simplified Treatment Guideline	December 2020	60	National Policy	A four-step simplified treatment guideline was enacted in the 2019 Nigeria Hypertension Protocol.	Medications data collected in the registry are used to calculate adherence to the four-step protocol by site, and across the program. In interim and final qualitative evaluations, sites will be asked for their feedback on the treatment guideline (appropriateness, feasibility, and adaptation).
Fixed-dose combination	December 2020	60	Health System	Fixed-dose combinations are encouraged in the hypertension treatment guideline when available.	Medications data collected in the registry are used to evaluate administration of fixed-dose or single pill prescriptions by site, and across the program. In interim and final qualitative evaluations, site will be asked for their feedback on fixed-dose combinations (appropriateness, feasibility, and adaptation).
Access to Essential Medicines and Technology	December 2020	60	Health System	Initial hypertension drug supplies were provided to all participating sites to prime the Drug Revolving Fund. During the first year of the intervention phase, work was completed to enact agreements for provision of hypertension medications at reasonable cost. The study team developed protocols, strategies, and training for adding hypertension medications to the Drug Revolving Fund.	Implementation of the Drug Revolving Fund will be evaluated in a separate protocol through RE-AIM outcomes. Early access to medicines in the study is evaluated through treatment rates, as well as stockout and replenishment rates at the participating sites.

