### Implementation strategies

Strategies to implement the package were identified based on barriers and facilitators mapping during the formative phase, previous implementation experience, mid-term qualitative evaluation, and ongoing stakeholder and site feedback (Table 2).

**Table 2 Tab2:** Hypertension Treatment in Nigeria Program contextual factors and implementation strategies

Strategy for Implementing HTN Program	Level of implementation	Description	Implementation package component supported
*Use evaluative and iterative strategies*			
Assess for readiness and identify barriers and facilitators	Health facility	Formative work included quantitative evaluation of site-level readiness and capacity and qualitative evaluation of barriers and facilitators to implementation.	• Hypertension patient registry and empanelment • Team-based care and community health extension worker provided hypertension management
Audit and provide feedback	Health facility	Performance and quality reports are provided to each participating site on a monthly basis. Supportive supervision visits are performed quarterly (minimal semi-annually).	• Performance and quality reporting
Conduct local needs assessment	Program	A service availability and readiness assessment was performed during the formative phase of the HTN Program alongside qualitative evaluation of stakeholder (healthcare workers, supervisors, and patients) needs. For the duration of the program, stakeholders have been engaged through an advisory board, including a patient representative.	• Hypertension patient registry and empanelment • Team-based care and community health extension worker provided hypertension management • Access to essential medicines and technology
Develop and implement tools for quality monitoring	Health facility and Program	Simplified performance and quality reports were adapted from the WHO HEARTS reporting tools to focus on improving quality of care based on key indicators of hypertension treatment, control, and patient retention.	• Hypertension patient registry and empanelment • Performance and quality reporting • Fixed-dose combination
Involve patients/consumers and family members	Program	Patients were engaged in focus group discussions during the formative phase and during the interim and end-of-study assessments. A local patient representative sits on the advisory committee.	• Hypertension patient registry and empanelment
*Provide interactive assistance*			

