Develop educational materials	Program	Contextually appropriate patient handouts and instructional materials were developed by the study team. Handouts depict the importance of health diets, regular physical exercise, smoking cessation, minimizing alcohol intake, weight loss, medication adherence and regular blood pressure checks. Community awareness campaigns are conducted in each area council to increase awareness of and demand for hypertension services.	• Simplified treatment guideline • Team-based care and community health extension worker provided hypertension management
Distribute educational materials	Health facility	Patient handouts are distributed by health educators during community awareness programs and by CHEWs during blood pressure screening visits within the PHCs.	• Hypertension patient registry and empanelment
Make training dynamic	Program	Demonstration-based learning techniques are used to reinforce information and methods for hypertension diagnosis, treatment, and management.	• Team-based care and community health extension worker provided hypertension management
Provide ongoing consultation	Health facility	Supportive supervision visits are conducted at least semi-annually to each participating health facility. Initial and ongoing training is provided to participating healthcare centers and CHEWs on the implementation components.	• Performance and quality reporting • Simplified treatment guideline • Team-based care and community health extension worker provided hypertension management
*Support clinicians*			
Create new clinical teams	Health facility	Team-based care (CHEWs, CHOs, Physicians, Medical Record Officers, Pharmacy Technicians, etc.) was provided at participating PHCs, focused on infectious diseases and maternal care. New teams specifically focused on hypertension care were formed or adapted for the HTN Program.	• Team-based care and community health extension worker provided hypertension management
Revise professional roles	Program	Encourage implementation of team-based care and task sharing.	• Team-based care and community health extension worker provided hypertension management
*Engage consumers*			
Increase demand	Health system	Conduct community outreach and mobilization activities to increase awareness and demand for hypertension services.	• Hypertension patient registry and Empanelment • Community awareness and mobilization campaigns

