### Monitoring

We have performed central statistical monitoring to evaluate sites’ performance and to direct risk-based, in-person, site monitoring and supportive supervision visits. In-person site monitoring visits have been conducted at minimum every 6 months with a target for quarterly visits for most sites. In-person visits are performed by at least two members of the HTN Program study team. Supportive supervision visits follow a checklist (Additional file 7) including quantification of site staff, inventory of equipment, observation of blood pressure measurement, and audit of patient paper case report forms. All site monitoring data are entered within a central REDCap database and summarized on a monthly basis to identify data quality problems, urgent staff or equipment needs, or other major data status or quality trends.

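### The audit-report and supervision fidelity items in Table 3 use windows longer than the program's own delivery schedule, so they are insensitive to partial delivery failure

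*Protocol article*

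**What the plan says.** Table 3 describes the Implementation domain as fidelity to the program protocol and includes in it whether delivery was consistent and as planned. Two of its program-level quantitative items concern delivery to sites:

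- Reports: "Proportion of selected PHCs who received an audit and feedback report within the past 3 months".
- Supervision: "Proportion of selected PHCs who received at least one supportive supervision visit in the past 7 months".

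The planned delivery is set out elsewhere in the article:

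- Reports are monthly. Table 1 says "Monthly performance and quality reports are issued to each participating site to summarize key metrics, aggregated over a rolling 3-month period", and Table 2 (audit and feedback) says "Performance and quality reports are provided to each participating site on a monthly basis".
- Supervision is quarterly by target with a half-yearly floor. Table 2 (audit and feedback) says "Supportive supervision visits are performed quarterly (minimal semi-annually"; Table 2 (ongoing consultation) says "Supportive supervision visits are conducted at least semi-annually to each participating health facility"; the Monitoring section says "In-person site monitoring visits have been conducted at minimum every 6 months with a target for quarterly visits for most sites".

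The Primary outcomes section lists implementation among the co-primary implementation outcomes. Table 3 also plans to examine why the fidelity measures vary.

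**The concern.** A fidelity item should compare what was delivered with what was due. Here the scoring windows are longer than the intervals in the schedule: three months for something due monthly, and seven months for something due quarterly by target and every six months at the least. A site can fall short of the schedule and still be counted as having received it in full.

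What is at stake is how the implementation results are read. If partial delivery is scored as adherence, the program may report high fidelity for audit and feedback when sites received only some of their reports. The difference between a fully served and a partly served site would also be compressed, and the trial needs that difference to explain variation between sites and to advise on scale-up.

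**Working it through.** The plan gives no figure for these items, so there is none to reproduce. The check counts deliveries due per scoring window.

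**Inputs**
- Report window: 3 months, with a report read as at least one (Table 3).
- Report schedule: one per site per month (Tables 1 and 2).
- Visit window: 7 months, at least one visit (Table 3).
- Visit schedule: quarterly target, 6-month minimum (Table 2, Monitoring).
- Intervention phase: 37 months, December 2020 to December 2023 (Timeline).

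**1. Reports, evenly spaced misses**
- Due per window: 3. Needed to pass: 1. Share that can be missed: 2/3.
- One report every third month over 37 months gives 13 reports if the first falls in month 1, and 12 if it falls in month 2 or 3.
- Delivered: 12/37 = 32% to 13/37 = 35%. Missed: 24/37 = 65% to 25/37 = 68%.
- Full 3-month windows end in months 3 to 37, which makes 35. Each holds exactly one report, so the site passes at 35 of 35.

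**2. Reports, random misses**
Assume each monthly report arrives independently with probability p. The documents do not give p.
- Expected score on the Table 3 item: 1 − (1 − p)³.
- Probability that all three due reports arrive: p³.

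| p | Table 3 item | All three received |
|---|---|---|
| 1/3 | 1 − (2/3)³ = 70.4% | (1/3)³ = 3.7% |
| 0.5 | 1 − 0.5³ = 87.5% | 0.5³ = 12.5% |
| 0.8 | 1 − 0.2³ = 99.2% | 0.8³ = 51.2% |

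At each of these rates the item stands well above p itself.

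**3. Supervision visits**
- Visits due in 7 months: 7/3 = 2.3 on the quarterly target, 7/6 = 1.2 on the 6-month minimum.
- A site visited every 7 months receives 3/7 = 43% of the quarterly target and 6/7 = 86% of the minimum.
- Full 7-month windows end in months 7 to 37, which makes 31. Counted month by month, a site visited every 6 months and a site visited every 7 months both pass at 31 of 31. A site visited every 8 months passes at 27 of 31.
- The item therefore does not separate a 7-month interval from a 6-month one, but it begins to register failure at 8 months.

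**4. Other items**
No other quantitative item in Table 3 sets reports or visits delivered against those due. The monthly fidelity items at center level concern stepped care and fixed-dose combinations.

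**The case against.** The strongest reply is that these are recent-receipt indicators, and that a delivery ratio is a measurement preference. The report window has some basis in the article: each report summarizes a rolling three months, so one per quarter still spans the data; Table 1 has the study team follow up on the reports with sites quarterly; and the adoption items also look back three months. This explains how the window may have been chosen. It does not alter that delivery is specified as monthly, and delivery is what this domain is meant to measure.

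On supervision the reply is stronger. Seven months is only one month past the floor and may be a grace period, although the text does not say so. Table 2 says semi-annually, which one visit in each half-year could satisfy despite a gap of more than six months; only Monitoring states a 6-month interval. Monitoring also limits the quarterly target to most sites, so the 43% does not apply to every site. All of this stands, and the supervision part is the weaker one.

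The reply also limits the consequence. These are two of several fidelity items, and the article attaches no test or success threshold to them. Visit data are held in the central REDCap database and summarized monthly, so adherence to the visit schedule can be tracked anyway.

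A reader might go further and infer that the items cannot register delivery failure, or that they read near 100% whether a site got all its reports or a third. The documents do not support that. Both items flag a site with no report for more than three months or no visit for more than seven. A site at one-third delivery always passes only if its reports are evenly spaced; random misses at that rate give about 70%. Each site is scored yes or no, so 100% is properly a statement about the program proportion, or about one site over repeated assessments.

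**Conclusion.** The mismatch between the scoring windows and the delivery schedule is in the text and needs no assumption: two of three monthly reports can be missed without losing adherence, and the visit window exceeds the stated 6-month minimum by one month with no grace period given. The item is exactly blind to one-third delivery only under even spacing. The figures of about 70% at one-third delivery and 99% at 80% delivery rest on independent random misses, and the actual delivery rate is unknown.

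The items are thus insensitive to partial failure while still detecting long gaps. The report item is the main problem; the supervision item chiefly needs its window explained or aligned. The effectiveness analyses and the sample size are not touched. This is an inexpensive improvement to a domain that the trial labels co-primary, and it should be made.

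**What to change.** 1. **Reports.** Add, overall and per site, reports issued divided by site-months due. With 60 sites and a report due in each of 37 months, the overall denominator is at most 60 × 37 = 2,220 site-months.
2. **Supervision.** Score the item against the 6-month minimum, or state that the 7-month window includes a one-month grace period. Report visits made over quarterly visits due descriptively, only for the sites that have the quarterly target, and identify those sites.
3. **Current items.** Keep both as a lenient version, labelled as such.

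The cost is a change of wording in Table 3 and slight re-tabulation. Site-monitoring data are already in the central REDCap database, and a record of the monthly reports issued should be easy to assemble. The one downside is that reported fidelity may come out lower.

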### Participants

Prior to study initiation, we identified and assessed all public primary healthcare centers within the Federal Capital Territory of Nigeria (*N*=243) based on staffing, patient volumes, and functionality. To be eligible, primary healthcare centers had to have at least two full-time staff, be accessible to the study team by road and in all seasons, and be functional (i.e., defined as open at least between the hours of 8 AM and 4 PM and providing the minimum service package for primary healthcare centers). Sites were randomly selected through a multi-stage sampling frame including stratification by caseload and geography. Selected primary healthcare centers were invited to participate in the program, and all 60 (100%) of invited sites agreed to participate. Each selected primary healthcare center participated in a hypertension-adapted Service Availability and Readiness Assessment (SARA) based on the WHO instrument prior to initiation of the control phase to evaluate and confirm capacity and readiness for the study [19].

During the control and intervention phases, all adults (≥ 18 years) who presented at a participating site with persistently elevated blood pressure (systolic blood pressure ≥ 140 mmHg or diastolic blood pressure ≥90 mmHg, measured twice) or a history of hypertension were eligible for inclusion. Patients were registered in the study database through entry in a site-based patient registry log and empaneled in the hypertension cohort (Additional file 3). Informed consent was not collected per the Common Rule [20].

We collected data on paper case report forms, which were designed to be included in the patients’ medical files at each primary healthcare center (Additional file 4). Paper case report forms are completed and maintained by the CHEW at registration and each subsequent patient visit. After the patient visit, a record information officer at the site abstracted information from the patient case report form into the electronic REDCap database [21]. The REDCap database was hosted at the University of Abuja, and each participating primary healthcare center was provided with a tablet upon which the REDCap mobile application was installed. Data capture included, but was not limited to socio-demographics, medical history, anthropometrics, blood pressure values, relevant laboratory studies when available (e.g., serum potassium, serum creatinine), medications, side effects, adverse events, counseling, and patient vital status.

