### Intervention

The implementation package components were informed by the KPNC intervention toolkit and WHO HEARTS technical package (Fig. 1). To adapt the implementation package, we performed formative in-depth interviews and focus group discussions with patients, healthcare workers, and administrative staff to identify facilitators, barriers, and context to implementation of hypertension services within primary healthcare centers in the Federal Capital Territory, Nigeria [17]. The final implementation package includes a hypertension patient registry (health system level), performance and quality reporting (health clinic level), simplified treatment guidelines (national policy level), fixed-dose combination therapy (health system level), access to essential medicines and technology (health system level), team-based care and non-physician follow-up (health worker level), and health coaching and home blood pressure monitoring (patient level), all of which have demonstrated improved population-level hypertension control in other settings (Table 1) [3, 22, 23].

**Table 1 Tab1:** Hypertension Treatment in Nigeria Program implementation package

Component	Start date	Number of sites	Level of intervention	Description as used in the HTN Program	Evaluation
Hypertension Patient Registry and Empanelment	January 2020	60	Health System	Paper-based registration and case report forms facilitate site-based tracking and follow-up of patients, aligns with existing practices for health record management, and are easy to implement. The electronic database facilitates rapid roll up of information in a structured database with built-in quality assurance checks.	Supportive supervision visits include comparison of the site visit logs and the hypertension registry to evaluate completeness of the registry. Bi-weekly data and safety quality reports are generated to review electronic data. Central and on-site training and reinforcement are provided, including the latter during site supervision visits to register all adult hypertensive patients.

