### Outcomes

#### Primary outcomes

The study’s co-primary implementation outcomes include reach, effectiveness, adoption, implementation, maintenance, acceptability, and cost of the multi-level hypertension control program. The study's co-primary effectiveness outcomes are the change in slope from baseline slope of monthly hypertension treatment rates (defined as using any blood pressure-lowering drug) and monthly hypertension control rates (defined as systolic blood pressure <140 mmHg and diastolic blood pressure <90 mm Hg) among participating primary healthcare centers. We chose this definition of control based on the 2019 Nigeria Hypertension Protocol.

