### Sample size

To estimate our sample size calculated for the primary effectiveness outcome, we used data from published literature to estimate the baseline prevalence of hypertension treatment (20%) and control (10%) rates in the Federal Capital Territory, Nigeria [25]. We based the anticipated effect on similar programs, including the KPNC Hypertension Control Program [2]. The power and sample size were estimated under a variety of conditions through Monte-Carlo simulation in SAS (v9.4, SAS Inc, Cary, North Carolina). Accounting for 10 sites dropping out, we estimated that 1200 patient visits per month across 50 sites over 9 months of baseline and 39 months of intervention would provide >80% power to detect a difference in treatment slope of 0.57% per month compared to underlying trend of 0.10% per month, resulting in hypertension treatment rate of 42.5% at the end of 48 months. Similarly, with the same sample size, we would have >80% power to detect a difference in control slope of 0.44% per month compared to underlying trend of 0.05% per month, resulting in hypertension control rate of 27.0% at the end of 48 months.

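### The registration-fidelity item in Table 3 puts its numerator and denominator on different bases, so it is not a true coverage proportion

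*Protocol article*

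**What the plan says.** Table 3, Implementation domain, center level, Fidelity (Intervention), gives the item as "Number and proportion of adult patients with hypertension who are registered/total number of adult patients with elevated blood pressure within participating PHCs", with a window of the past 3 working days.

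The Participants section sets who may be registered. Adults qualify on persistently elevated pressure, at least 140 mmHg systolic or 90 mmHg diastolic, "measured twice) or a history of hypertension were eligible for inclusion". Table 1 describes training and supervision meant to get sites to "register all adult hypertensive patients", which is wider than those whose pressure is raised on the day.

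The Primary outcomes section defines control as "systolic blood pressure <140 mmHg and diastolic blood pressure <90 mm Hg". A hypertensive patient can therefore be in the registry without having elevated pressure at a given visit.

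The qualitative item paired with this one in Table 3 asks why adults with hypertension were not registered in the same 3-day window. It uses hypertension, not elevated pressure, as its base. The article gives no expected value, target or sample size for the quantitative item.

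**The concern.** A fidelity measure for registration should say what share of the patients who ought to be registered actually are. For that, everyone in the numerator must also be in the denominator. Here the two parts name different groups, and nothing in the article restricts the numerator to patients with elevated pressure.

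The mismatch works both ways. Controlled and history-only registrants enlarge the numerator alone. The denominator as worded does not require two readings, so adults with one raised reading and no history enlarge the denominator alone.

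This matters because implementation is among the named co-primary implementation outcomes, and this item addresses whether hypertensive attenders reach the registry. The effectiveness series is built from visits recorded in the database, so readers will want to know how complete registration is. A ratio that shifts with the control rate is a poor guide to that.

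**Working it through.** There is no stated figure for this item to reproduce, so the check is algebra on the definition.

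**Inputs**
- H: hypertensive adults attending in the window. It cancels.
- r: share of H who are registered. Not in the documents; assumed 80% for the main illustration.
- c: share of H with pressure below 140/90. Illustrated with the Sample size section's planning rates: 10% at baseline ("estimate the baseline prevalence of hypertension treatment (20%) and control (10%) rates") and 27% at the end ("resulting in hypertension control rate of 27.0% at the end of 48 months").
- f: non-eligible adults with an elevated reading, per hypertensive attender. Not in the documents; assumed 0, 0.1 and 0.2.

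The 27.0% is close to what the section's slopes give when 0.44 is read as the intervention-phase slope: 10 + 8×0.05 + 38×0.44 = 27.12, or 10 + 9×0.05 + 39×0.44 = 27.61. That is near enough for an illustration.

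**Formula.** If all registered hypertensive attenders are counted:

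ratio = rH / [(1 − c)H + fH] = r / (1 − c + f)

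**Results for r = 80%**

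| f | c = 10% | c = 27% |
|---|---|---|
| 0 | 0.80/0.90 = 89% | 0.80/0.73 = 110% |
| 0.1 | 0.80/1.00 = 80% | 0.80/0.83 = 96% |
| 0.2 | 0.80/1.10 = 73% | 0.80/0.93 = 86% |

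**Direction of error.** The ratio is above r when f < c, equal to r when f = c, and below r when f > c. At f = 0.2 it understates 80% coverage at c = 10% (73%) and overstates it at c = 27% (86%).

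**When it exceeds 100%.** This needs r > 1 − c + f.

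| f | Threshold for r at c = 10% | Threshold for r at c = 27% |
|---|---|---|
| 0 | 90% | 73% |
| 0.1 | 100% (cannot be exceeded) | 83% |
| 0.2 | 110% (unreachable) | 93% |

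**Drift with control at fixed r.** The ratio is multiplied by (0.90 + f)/(0.73 + f). This is 0.90/0.73 = 1.23 at f = 0, 1.00/0.83 = 1.20 at f = 0.1, and 1.10/0.93 = 1.18 at f = 0.2. Registration has not changed in any of these cases.

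**If only new registrations count.** Take 10 new registrants, 2 of them entered on history with normal pressure. With no already-registered patient with elevated pressure attending, the ratio is 10/8 = 125%. With 20 such patients it is 10/28 = 36%. The numerator is still not contained in the denominator, but the link with control is weaker and need not take the form above.

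**With one base.** Registered hypertensive attenders over all hypertensive attenders equals r. At r = 80% that is 80% at both control rates, and it cannot exceed 100%.

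**The case against.** The strongest reply is that a compressed table cell is being read too literally. The item is called a proportion, and the Reach item on blood pressure measurement has the same form, with a numerator that naturally sits inside its denominator. Read that way, the fidelity item asks how many adults with elevated pressure in the last 3 working days are registered. It is then bounded by 100% and has no built-in link to control. Elevated pressure may also be loose wording for hypertension, and the supervision checklist (Additional file 7, not shown) may hold the counting rule.

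These readings are possible, but each has to be supplied by the reader. The article treats hypertension and elevated pressure as different groups in its eligibility and control definitions, and the paired qualitative item uses hypertension. If the subset reading is intended, the wording still needs correcting.

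Other parts of the reply stand. Neither r nor f is in the documents, and f pulls the ratio down: the 110% appears only at f = 0. The 10% is a literature estimate for the Territory and the 27% a projection for program visits, whereas c should describe all hypertensive attenders, registered or not.

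A reader might infer that the item will exceed 100%, or that its time trend will be confounded with the effectiveness outcome. The documents do not support either. Exceeding 100% depends on unknown quantities. No trend analysis, test or threshold is stated for this item, which is a 3-day count, unlike the two monthly items beside it.

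**Conclusion.** The point holds for the definition as written. The two parts of the ratio do not share a base, so it does not measure registration coverage. It can err up or down and can exceed 100%. At 80% assumed coverage, with c at 10% or 27% and f from 0 to 0.2, it reads anywhere from 73% to 110%. The rise with control, by a factor of 1.18 to 1.23 over that range, also assumes that all registered attenders are counted and not only new registrants.

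The weight is limited. This is one descriptive measure among many in Table 3. A reader might infer that the main effectiveness result is compromised. It is not: the co-primary treatment and control slopes do not use this ratio, and neither does the sample size.

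**What to change.** State one base and the same 3-working-day window for both parts. The preferred form is: registered adult attenders who meet the Participants criteria (persistently elevated pressure measured twice, or a history of hypertension), divided by all adult attenders who meet them. This matches the paired qualitative item and the aim of registering all hypertensive adults. The text should also say whether patients registered before the window count in the numerator; for a coverage measure they should.

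The article does not show whether site visit logs record hypertension history. If they do not, use registered adults with elevated pressure over all adults with elevated pressure, and label the result as that narrower measure. It says nothing about controlled or history-only patients.

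The cost is a change of wording to one indicator and at most a small extra tally at supervision visits, which already compare visit logs with the registry.
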